##### 4. HRQoL for economic evaluation

The Foundation for the National Institutes of Health Biomarkers Consortium Project Team and the FDA have explicitly indicated that patient-reported outcome measurements, or how a patient “feels and functions,” are important, required by regulation, and should be measured at early and late time points. However, no RCT included in the Cochrane review of cellulitis treatment assessed HRQoL [6]. The planned study aims to measure HRQoL using the EQ-5D-5L instrument and also to validate a novel disease-specific HRQoL instrument, the ESTI score, in order to address these knowledge gaps. Validation of the ESTI score may also inform future health care decisions about more costly interventions for the treatment of cellulitis. In the meantime, a large proportion of the economic cost of skin and soft tissue infections (SSTIs) caused by community-acquired methicillin-resistant *Staphylococcus aureus* (CA-MRSA) stems from losses in patient productivity [7]. However, the economic impact of treating ABSSSI for patients presenting to EDs is unknown; by performing a pharmacoeconomic analysis we will provide useful insights regarding the economic impact of treating this relatively common ED condition.

The EQ-5D-5L has been selected as the most appropriate measure of HRQoL. It is a standard measure of self-reported HRQoL which includes five domains: mobility, self-care, usual activities, pain/discomfort and anxiety/depression. The ESTI score will also be measured and mapped against the ED-5D-5 L as a robustness check and this outcome will be used as an alternative way to measure QALYs. The EQ-5D-5L, the 12-Item Short Form Health Survey (SF-12) and ESTI score will be used to obtain patient reports of HRQoL and then used in the estimation of QALYs. The (SF-12) instrument is routinely used as a sensitivity check for quality of life within trials.

##### 5. Pharmacoeconomic analysis of cost per QALY

Although the cost of treating cellulitis may be relatively low, it is important to understand the full health outcomes associated with acute cellulitis in order to establish complete cost-effectiveness for resource allocation decisions. We will perform a within-trial economic evaluation of the cost per QALY gained from the use of orally administered flucloxacillin alone compared with using combination therapy of orally administered flucloxacillin and phenoxymethylpenicillin over a 1-month time horizon from the perspective of the health care payer (direct costs). The QALY measure captures the impact of a treatment on a patient’s length of life and also the impact on their HRQoL and is widely used in health economics as a summary measure of health outcome, which can inform health care resource allocation decisions.

In a secondary analysis the perspective will be extended to consider costs related to the intervention falling on the patient and the government. Costs will be estimated from recorded resources used during the trial, and from health care utilisation and absenteeism/productivity (for the broader perspective) data collected from patients using questionnaires administered at all time points. The EQ-5D-5L, (SF-12) and ESTI score will be used to obtain patient reports of HRQoL and used in the estimation of QALYs. The health economics study aims to identify the within-study incremental cost-effectiveness ratio (ICER; i.e. the costs and benefits of the treatment compared to the control group). Cost per QALY will be the main outcome derived.

### Data collection

An electronic Case Report Form (eCRF) will be used to collect all data. For a paper version of this CRF (paper CRF or pCRF; see Additional file 1). Briefly, in addition to the outcome measures specified above, demographics, including age, gender (male/female), ethnicity (White/Black/Asian/Other) and current smoker (yes/no), vital signs including blood pressure, heart rate, temperature, level of alertness, and previous medical history (including history of cardiac disease, diabetes, vascular disease, venous insufficiency, any other diseases) and Charlson Comorbidity Index (CCI) will be collected.

Data on health resource use costs and quality of life will also be collected (see Additional files 2 and 3). The latter will be used to calculate QALYs for the pharmacoeconomic analysis. The CRFs will include a health resource use questionnaire that will be adapted from the standard Client Service Receipt Inventory (CSRI) that is used in trials to collect information about extra resource utilization (e.g. general practitioner visits), medication use, work status and payment of health costs. Patients will receive this at each time point in the trial. Unit costs will be retrieved from Irish and United Kingdom (UK) reference costs. Medication costs will be taken from the Health Service Executive (HSE) Primary Care Reimbursement Service database. The HSE is the statutory provider responsible for all the public health and social services in hospitals and in the community in the Republic of Ireland. Life years gained will be extracted from the published literature. Costs will also include treatment costs. The costs to patients, in terms of time input and travel expenses over the course of the trial, will be estimated. These costs will reflect real-life expenditure post trial. There are still no reference costs available in Ireland (similar to the National Health Service unit costs and Personal Social Services Research Unit costs in the UK), so we will collect unit cost data for relevant resource items from local data sources and expert opinion, or from similar utilisation in the UK if none are available in Ireland. All costs will be up-rated to 2017 prices using the health component of the consumer price index in Ireland. Pounds will be converted to euros using the 2017 exchange rate from the Central Bank of Ireland.

All data being entered into the eCRF will be validated according to agreed criteria appropriate to the data type (i.e. upper and lower limits on numeric values and dates, drop-down lists of valid responses or radio-button selection for multiple option items, dependency-driven data items will only be collected where necessary and relevant).

### Analyses sets/populations/subgroups

For the analysis of the primary outcome both intention-to-treat (ITT) and per-protocol (PP) analyses will be performed. Initially, ITT analyses will be performed and will include all patients randomised to the trial regardless of whether they have taken the study drug or not. PP analysis will be defined as in a previous randomised controlled trial for uncomplicated skin abscesses conducted by Talan et al. in the United States [8]. It will include participants who either took ≥ 75% of the total doses of study drug or placebo during the first 5 days and had an in-person test-of-cure visit or were determined to have had clinical failure before the test-of-cure visit and received ≥ 75% of the doses provided during the first 48 h of the treatment period. In a non-inferiority trial setting it is suggested that a PP analysis may be more appropriate than ITT since it is more likely to reflect actual differences between the two treatments [9]. Furthermore, ITT analysis may be interpreted as being too liberal in a non-inferiority trial and may bias toward making the two treatments appear similar. As a result, both an ITT and PP analysis will be performed on the resulting data to assess non-inferiority. Non-inferiority will only be declared if both ITT and PP analysis support non-inferiority.

### Handling of missing data values

Any missing data or data anomalies will be communicated to the study site(s) for prompt clarification and resolution. It is not anticipated that there will be a huge amount of missing data. However, in the unlikely event that there is more than 10% of data values missing, missing values will be imputed, if possible, using a suitable imputation method.

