### Determination of sample size

The sample size per trial arm was calculated based on an assumed treatment success rate of 85% with orally administered flucloxacillin and phenoxymethylpenicillin, a non-inferiority threshold *Δ* = 12.5% and *α* = 0.025 (as this is a non-inferiority study). Sample sizes were calculated using SAS v9.3 (SAS Institute Inc., Cary, NC, USA). Given the preferred study power of 90% for non-inferiority trials and a clinical evaluability rate of 80%, it is estimated that a minimum sample size of 207 in each treatment arm is required (*n* = 414).

The non-inferiority margin was based on a combination of statistical reasoning and clinical judgement. The non-inferiority margin of 12.5% was considered clinically acceptable based on best current evidence [3]. Additionally, the Infectious Diseases Society of America has recommended a non-inferiority margin of between 10 and 15% for RCTs of antibiotic treatment for cellulitis [4]. Furthermore, current RCT evidence indicates that the efficacy of the comparator intervention (i.e. dual therapy with flucloxacillin and phenoxymethylpenicillin) is 83–87% efficacious. Our sample size for each trial arm was calculated based on an assumed treatment success rate of 85%, which is the midpoint of this 83–87% success range.

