### Primary endpoint

Non-inferiority of the primary outcome measure, the percentage of patients cured on day 14–21, will be assessed by calculating a two-sided 95% confidence interval (CI) on the difference of proportions between the two trial arms. Only one side of the confidence interval is of interest; this equates to a one-sided test with alpha at 0.05/2 (i.e. 0.025). If the upper limit of the CI is less than the non-inferiority margin threshold of 12.5%, then non-inferiority will be inferred.

Secondary analyses will investigate the effects of further adjustment for any variables displaying marked imbalance between the arms at baseline.

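### The imputation trigger leaves missing test-of-cure outcomes without a rule at or below 10%, so the ITT analysis of all randomised patients can become a complete-case analysis by default

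*Protocol article*

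**What the plan says.** Under *Analyses sets/populations/subgroups* in the Protocol article, the ITT analysis "will include all patients randomised to the trial regardless of whether they have taken the study drug or not". The same section requires both the ITT and the per-protocol (PP) analysis to support non-inferiority before it is claimed. PP membership needs a dose threshold plus an in-person test-of-cure (TOC) visit, or an earlier clinical failure with its own dose threshold.

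*Handling of missing data values* expects little missing data and then states that "in the unlikely event that there is more than 10% of data values missing, missing values will be imputed, if possible". The method is described only as suitable.

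*Primary endpoint* puts a two-sided 95% confidence interval on the difference in the percentage cured and compares its upper limit with 12.5%. *Trial profile, recruitment and retention* foresees exclusions from the primary analysis and says that the reasons will be reported. *Sensitivity analyses* contains one item, which removes telephone follow-up. *Determination of sample size* uses "a clinical evaluability rate of 80" per cent, without defining evaluable.

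**The concern.** The plan states a rule for missing data, and the rule stops short of the case that matters. When 10% or less is missing there is no imputation, and no other instruction replaces it: not failure, not exclusion, not a best-available assessment. A confidence interval on proportions then uses whoever has an outcome, and that is not every randomised patient. When more than 10% is missing, the method is unnamed and conditional on being possible, so it would be settled once the extent of the loss is known.

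ITT is one of two gatekeeping analyses. If patients who did badly are lost more often from the monotherapy arm, leaving them out makes the arms look more alike, which is the wrong direction for error in a non-inferiority trial. The PP analysis gives no independent check, because a patient with no TOC visit and no earlier failure is outside that set too. The telephone sensitivity analysis removes further patients and tests no assumption about those missing.

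**Working it through.** **Inputs from the Protocol article.** Dual-therapy success 85%, margin 12.5 points, one-sided alpha 0.025, 90% power, 80% evaluability, 207 per arm (414 in total), imputation threshold 10%. **Assumptions of this review:** equal true cure for the sample-size check, the split of missing patients between arms, observed cure in each arm, and cure among the missing. Differences are dual minus monotherapy, which fits the plan's use of the upper limit.

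**1. The plan's sample size.** n = 2 × 0.85 × 0.15 × (1.960 + 1.282)² / 0.125² = 171.5, so 172 evaluable per arm. 172 × 1.2 = 206.4, rounded up to 207, matches the stated figure; 172 / 0.8 = 215 does not. With 80% of 207 evaluable (165.6 per arm) power is 89.0%. That is a separate and small matter. It does show that 20% non-evaluability entered the planning.

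**2. Patients who can fall outside the rule.** 10% of 414 = 41.4. If the threshold refers to primary outcomes over both arms, up to 41 patients can be missing without imputation. On other readings of the denominator the number differs.

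**3. Can the conclusion turn on the missing rule?** Upper limit = d + 1.96 × √[p₁(1−p₁)/n₁ + p₂(1−p₂)/n₂]. Observed cure is about 85% in each arm, rounded to whole patients.

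*29 missing on monotherapy, 12 on dual (41 of 414 = 9.9%)*
- Patients with outcomes only: 151/178 = 0.848 v 166/195 = 0.851; d = 0.0030, SE = 0.0370, upper limit 0.0030 + 0.0726 = **7.6%**.
- Missing as not cured: 151/207 = 0.729 v 166/207 = 0.802; d = 0.0725, SE = 0.0415, upper limit 0.0725 + 0.0813 = **15.4%**.
- With exactly 85% in place of whole counts, the limits are 7.3% and 15.1%.

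*20 missing in each arm (40 of 414 = 9.7%)*
- Patients with outcomes only: 159/187 in each arm; d = 0, SE = 0.0369, upper limit **7.2%**.
- Missing as not cured: 159/207 in each arm; d = 0, SE = 0.0415, upper limit **8.1%**.

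Unequal loss puts the two answers on opposite sides of 12.5%. Equal loss does not.

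**4. Type I error of the ITT test when missing patients are left out.** True cure is 72.5% v 85%, exactly at the margin. Cure among those observed = (p − m × c)/(1 − m), where m is the missing fraction and c the cure rate among the missing. For 13% and 6% missing with c = 40% and 60%: monotherapy (0.725 − 0.13 × 0.40)/0.87 = 0.774; dual (0.85 − 0.06 × 0.60)/0.94 = 0.866; apparent difference 9.2 points instead of 12.5. The error rates below are from 400,000 simulated trials per row, with a Wald interval and missing counts fixed below 10% overall.

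| Missing, mono / dual | Cure among missing, mono / dual | ITT type I error |
|---|---|---|
| none | – | 2.6% |
| 13% / 6% | 30% / 85% | 36.3% |
| 13% / 6% | 40% / 60% | 13.4% |
| 13% / 6% | 60% / 72.5% | 4.7% |
| 13% / 6% | 60% / 60% | 3.1% |
| 9.5% / 9.5% | 40% / 60% | 4.1% |
| 9.5% / 9.5% | 60% / 72.5% | 2.6% |
| 9.5% / 9.5% | 50% / 50% | 1.2% |

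**5. The two expectations about loss.** 20% of 414 = 82.8 non-evaluable patients, against a threshold of 41.4. If every non-evaluable patient had a missing outcome, the chance of passing 10% would exceed 0.9999. The article does not say that they would.

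**The case against.** The strongest reply has five parts.

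- **Complete-case analysis is nowhere stated.** That is correct: it is the consequence of a rule that stops at 10%, not a declared method. But the article presents itself as the detailed analysis plan, finalised before recruitment, so the gap is not plainly left to another document. Nor can missing-as-failure be presumed, because the primary outcome would then have nothing left to impute.
- **Recorded failures are already counted.** This stands. *Primary outcome measure* requires no failure at any previous visit for cure, and *Clinical treatment failure* classifies any failure up to TOC. Only patients lost without a recorded failure are exposed, which makes very low cure rates among the missing harder to defend.
- **The large error rates rest on stacked assumptions.** This also stands. The 13.4% and 36.3% rows need more than twofold differential loss in a double-blind trial, and no figure in the article supports it. If 13% and 6% were loss probabilities, about 35% of such trials would pass 10% and trigger imputation. The rates concern ITT alone; the joint rate with PP cannot be higher and was not computed.
- **The threshold need not pool the arms.** A reader might infer that it does and so overlooks unequal loss. The text names no denominator at all (per arm, overall, per variable or primary outcome), so pooling is one reading only.
- **20% non-evaluable is not 20% missing.** A reader might infer that calling more than 10% missing unlikely contradicts the sample-size assumption. It does not. Patients with too few doses, or followed only by telephone, can have a known outcome and still fail the PP definition.

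**Conclusion.** The point holds as a gap in a stated rule. At or below 10% missing, a randomised patient without a TOC outcome or an earlier recorded failure has no defined place in the ITT analysis and drops out by default, which does not fit the article's own ITT definition. Neither the PP analysis nor the telephone sensitivity analysis makes good the loss.

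The size is conditional. Just under the threshold, the non-inferiority conclusion can depend on the unstated rule when loss is unequal (about 7% against about 15%), and it is unaffected in the equal-loss example. Missing-as-not-cured is an extreme convention, so this contrast measures fragility and not bias. ITT type I error can rise well above 2.5% under adverse unequal loss, stay near it, or fall to about 1%. It would be wrong to quote the adverse rows as the expected inflation.

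The low missingness expected under *Handling of missing data values* is not reconciled with the 80% evaluability rate, and a sentence should explain how they relate. The main point does not depend on this. It is worth correcting before analysis, though it does not by itself invalidate the design.

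**What to change.** Delete the 10% trigger. State that:

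- the ITT analysis includes every randomised patient whatever the proportion missing, and a failure recorded before TOC counts as not cured, as the outcome definitions already imply;
- remaining missing TOC outcomes are handled by one pre-specified method, for example multiple imputation within arm from the randomisation strata, baseline lesion area and status at the early-response and end-of-treatment visits;
- two sensitivity analyses accompany it: missing counted as not cured, and a tipping-point analysis that varies the cure rate among the missing separately by arm and reports where the conclusion reverses.

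Add one sentence defining clinical evaluability and how the 20% divides between missing outcomes and other reasons for exclusion from PP. Other principled imputation models would serve equally well; what matters is that one is named in advance.

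The cost is plan wording, modest programming and possibly a slightly wider ITT interval. No new data are needed.

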## Description of statistical methods

Data analysis and reporting will proceed according to the Consolidated Standards of Reporting Trials (CONSORT) extension to non-inferiority and equivalence RCTs [10]. The trial statistician will be blinded to the group status.

### Trial profile, recruitment and retention

The flow of trial patients will be displayed in a CONSORT diagram [11]. The number of screened patients who fulfilled trial inclusion criteria, and the number included in the primary and secondary analyses, as well as all reasons for exclusions in primary and secondary analyses, will be reported in addition to those withdrawing consent and those lost to follow-up.

### Demographic and baseline characteristics

The first stage of analysis will be to use appropriate descriptive statistics to describe recruited individuals, and to investigate comparability of the trial arms at baseline. For categorical measures the number of patients and percentage will be presented, and for continuous scales the mean and standard deviation (SD) will be presented. For continuous scales which show evidence of, or are expected to show some skew, a median and interquartile range may also be presented, or substituted for the mean and SD.

### Primary endpoint

Non-inferiority of the primary outcome measure, the percentage of patients cured on day 14–21, will be assessed by calculating a two-sided 95% confidence interval (CI) on the difference of proportions between the two trial arms. Only one side of the confidence interval is of interest; this equates to a one-sided test with alpha at 0.05/2 (i.e. 0.025). If the upper limit of the CI is less than the non-inferiority margin threshold of 12.5%, then non-inferiority will be inferred.

Secondary analyses will investigate the effects of further adjustment for any variables displaying marked imbalance between the arms at baseline.

### Secondary endpoints

ECR measured on day 2–3 post enrolmentThe percentage of patients in each trial arm cured on day 2–3 will be assessed similar to the primary endpoint by calculating a two-sided 95% confidence interval (CI) on the difference of proportions between the two trial armsThe relationship between clinical measurements at ECR and TOC will also be investigated
Clinical treatment failureA participant with clinical treatment failure for the duration of the study will be censored and the distributions of the two trial arms of the trial will be compared using the logrank testAdherence and persistence of trial patients with antibiotic therapyInitially, appropriate descriptive statistics will be used to describe all measures of adherence. More specifically, the following will be calculated and compared between the two arms of the trial using appropriate statistical tests (e.g. two-proportions z-test, chi-squared test, Fisher’s exact test):The proportion of patients who took all doses as measured by self-report, pill count and MEMS® capThe proportion of patients who took more than 80% of doses as measured by self-report, pill count and MEMS® capUsing the MEMS® cap, the proportion of patient’s who took exactly four doses a day for the duration of the treatmentUsing the MEMS® cap to investigate dosage interval adherence by calculating the following:(i)The proportion of patients who took all doses within 2 h of the recommended 6-hourly interval(ii)The proportion of patients who took all doses within 4 h of the recommended 6-hourly interval
Using the MEMS® cap, a frequency table of number of days to discontinuationUsing the MEMS® cap only, a frequency table of various adherence levels (0–10%, 11–20%, 21–30%, etc.), ignoring timing interval, and the corresponding proportion of patients with clinical response will be constructed

Additionally, regression analysis will be used to investigate determinants of good adherence (defined as > 80% adherence) for each measure of adherence (self-report, pill count and MEMS® cap). Variables will include age, gender, ethnicity, disease severity, number of concomitant medicines, health care utilisation and the incidence of adverse drug reactions.4.HRQoL assessmentsHRQoL scores will be derived from the EQ-5D-5L, the (SF-12) and the ESTI score mapped onto the EQ-5D-5L. The ESTI score is a disease-specific HRQoL instrument developed to quantify patients’ subjective experiences associated with having an ESTI [12]. However, it has not been externally validated or used as an outcome measure for HRQoL assessment in a clinical trial evaluating different management strategies for ESTI. The objective of this substudy is to externally validate the ESTI score and use it as an RCT outcome measure. The feasibility and practicality of the ESTI score will be examined by looking at the response rate and the proportion of missing responses at all time points. Correlations between ESTI score responses and the relevant questions in the EQ-5D-5L and correspondence between overall scores obtained on the ESTI score and the EQ-5D-5L will be examined to assess the ability of the ESTI score to measure what is intended. The distribution of health states and the mean ESTI scores for all time points will be examined to see if the ESTI score differentiates between health states. One would expect the ESTI score to detect important changes in health and an improvement in the scores with time. This responsiveness or sensitivity to clinical change will be assessed by the mean change in score for a scale divided by the SD of the change. Values greater than or equal to 0.2, 0.5 and 0.8 indicate small, moderate and large clinical changes, respectively. This standardised method will allow comparisons to be made between the ESTI score and the EQ-5D-5L. Additionally, to examine if the ESTI score detects important changes in health, discriminant validity will be used. Briefly, discriminant validity will involve determining if using dichotomous outcome measures (20% or greater reduction in cellulitis lesion, yes/no; clinical treatment failure, yes/no; clinical relapse, yes/no; compliance with therapy, yes/no; and adverse events; yes/no) as a method of splitting the sample to determine if the ESTI score can detect a difference between groups. Linear regression analyses will also be used to develop a mapping relationship between the ESTI score and the EQ-5D-5L. The purpose of the mapping is to predict health utilities in other data sets and hence the accuracy of the model’s predictions will be assessed. Both the lowest and highest quartiles will be evaluated separately to see if errors are affected by the severity of the cellulitis5.Pharmacoeconomic analysisHRQoL scores will be multiplied by the duration of time spent in each health state, in order to generate QALYs. The area under the curve (AUC) approach will be used for estimating QALYs, assuming a linear transition between each follow-up time point. The AUC will be 21 days with time point at each follow-up having a utility score. Differences in mean costs and QALYs between the two arms of the trial will be estimated, accounting for differences in patient characteristics and baseline costs and QALYs. If one strategy is not dominant (less costly and more effective), the incremental cost effectiveness ratios (ICER) of the cost per QALY gained will be calculated and bootstrapped estimates (with replacement, 1000 estimates) of the sampling distribution of costs will be generated to explore the uncertainty around the ICER. A cost-effectiveness acceptability curve will be used to describe the probability that the cost per QALY gained from the within-trial analysis is cost-effective for a range of levels of willingness to pay the decision-maker (their ceiling cost-effectiveness ratio). The net benefit will be estimated at a level of willingness to pay from €20,000 to €45,000 (National Centre for Pharmacoeconomics). The calculation of QALYs will be conducted, using a measure of quality of life. In the analysis, the non-parametric bootstrap method will be used to produce a within-trial probabilistic sensitivity analysis of the ICER. A scatterplot of the cost-effectiveness plane, the 95% cost-effectiveness ellipse and cost-effectiveness acceptability curve will be presented.

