## Trial overview

The PEDOCELL trial is a multicentre, randomised, parallel-arm, non-inferiority trial which will be conducted in five hospitals in the Republic of Ireland (Beaumont Hospital, Connolly Hospital, Cork University Hospital, Mater Misericordiae University Hospital and Mercy University Hospital). It may be necessary to include two contingency sites, dependent on recruitment rates. Those sites are Our Lady of Lourdes Hospital in Drogheda and Midlands Regional Hospital in Tullamore. The trial consists of a 7-day intervention period and a 2-week follow-up period.

Measurements will be undertaken at four specific time points: at the baseline visit, at the early clinical response (ECR) visit on day 2–3 after enrolment, at the end-of-treatment (EOT) visit on day 8–10 post enrolment and at the test-of-cure (TOC) visit on day 14–21 post enrolment.

The study design also includes a substudy to evaluate patient adherence and persistence with therapy using an electronic MEMS® cap. The purpose of this substudy is to describe these parameters in the understudied area of short-course outpatient antibiotic treatment as well as to provide evidence for any adjustments in analysis based on medication-taking behaviour.

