### Interventions

Patients will be randomised in a blinded fashion to either orally administered flucloxacillin 500 mg and placebo, or orally administered flucloxacillin 500 mg and phenoxymethylpenicillin 500 mg, both four times daily for 7 days.

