##### 3. Adherence and persistence of trial patients with outpatient antibiotic therapy

Medication adherence will be measured at EOT in various ways:By self-reportHave you taken all of your antibiotic doses as prescribed? (yes/no)If not, how many times would you estimate you did not take your doses as prescribed?Did you finish your antibiotic course?If not, when did you stop? (day 0–7)
By counting the number of unused study medications at the EOT visit. Patients will be asked to bring their medication with them to the EOT visit so that a pill count can also be performedBy using an electronic monitoring system (MEMS® cap). The MEMS**®** cap will be used to measure adherence in a subset of 100 patients assigned to either treatment arm at the Beaumont Hospital study site only. The MEMS® cap will be fitted to the dispensed medication bottle. Patients will be informed that the cap will monitor each opening of the bottle and, as such, they should only open the bottle when they are about to ingest a dose. Any other openings should be recorded and the research team should be informed. The MEMS® cap should be returned with the clinical trials supplies on the follow-up visits

Medication persistence may be defined as the duration of time from initiation to discontinuation of therapy [5]. Persistence will be measured using the MEMS® cap in the subgroup of 100 patients. It will be measured by determining from the MEMS® cap report the time (in days) from the start day of treatment to the day of the last dose taken without regard for any missing doses or days in between. Missing doses and days will be described separately in descriptions of adherence.

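### The only MEMS dose-timing measures are all-or-none per patient: one lapse counts the same as erratic dosing, and the 2 h version risks a floor effect

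*Protocol article*

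**What the plan says.** The Interventions section gives the regimen in both arms as "both four times daily for 7 days". The section on adherence and persistence says that the MEMS cap "will be used to measure adherence in a subset of 100 patients assigned to either treatment arm", at one site.

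The Secondary endpoints section lists adherence measures to be calculated and "compared between the two arms of the trial using appropriate statistical tests". Two concern dose timing:

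- "The proportion of patients who took all doses within 2 h of the recommended 6-hourly interval"
- "The proportion of patients who took all doses within 4 h of the recommended 6-hourly interval"

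A third MEMS measure is the proportion of patients with four doses on every day of treatment. The section also plans graded summaries of how many doses were taken, but the banded MEMS table is "a frequency table of various adherence levels (0–10%, 11–20%, 21–30%, etc.), ignoring timing interval". The Trial overview describes the substudy as mainly descriptive: "The purpose of this substudy is to describe these parameters in the understudied area of short-course outpatient antibiotic treatment". It adds that the substudy should inform any analysis adjustments for medication-taking behaviour.

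**The concern.** Each timing measure reduces a week of time-stamped openings to one yes or no per patient, and the yes requires every dose to be on time. A patient with one lapse and a patient who doses erratically all week are both recorded as failures. The 2 h version has a further problem. A patient who takes four doses in waking hours and sleeps through the night can easily leave more than 8 h between the last dose of one day and the first of the next. That patient fails however regular the dosing is.

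At stake is whether the between-arm timing comparison in the substudy can show anything. If few patients in either arm pass the 2 h measure, a test on about 50 per arm will rarely detect a difference, and no planned graded measure would use the same timing data.

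**Working it through.** The article gives no expected rate, power or sample-size basis for the MEMS measures, so there is no stated figure to reproduce.

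**Inputs**
- Doses: 4 × 7 = 28, so 28 − 1 = 27 intervals (Interventions). Over seven days these are 7 × 3 = 21 daytime gaps and 6 overnight gaps.
- MEMS patients: 100 (adherence section). An even split of 50 per arm is assumed.
- Windows, read as gaps between consecutive doses: 6 ± 2 h = 4–8 h, and 6 ± 4 h = 2–10 h.
- Per-interval compliance p: not given, so a range is used.
- Test level: none is stated for these tests; two-sided 0.05 is assumed.

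**Step 1: a regular waking-hours pattern (illustration only).** Doses at 07:00, 12:00, 17:00 and 22:00 give gaps of 5, 5, 5 and 9 h. The 9 h gap exceeds 8 h, so the patient fails the 2 h measure every night. All four gaps lie within 2–10 h, so the same patient passes the 4 h measure. If the window is instead read against a fixed 6-hourly clock from the first dose (07:00, 13:00, 19:00, 01:00), the deviations are 0, 1, 2 and 3 h, and the result is the same: fail at 2 h, pass at 4 h.

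**Step 2: all-or-none pass rate if intervals are independent, p^27.**

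| p | 0.80 | 0.85 | 0.90 | 0.95 | 0.97 | 0.98 | 0.99 |
|---|---|---|---|---|---|---|---|
| p^27 | 0.2% | 1.2% | 5.8% | 25% | 44% | 58% | 76% |

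The pass rate is 5% or lower only if p is about 0.895 or lower (0.05^(1/27) = 0.895).

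**Step 3: simulation that treats overnight gaps separately.** Six overnight gaps had a mean of 6–9 h, with between- and within-patient SDs of 0.75 h. The 21 daytime gaps had an SD of 0.5–1 h. The chance of missing a dose was 0–5%, and any missed dose counted as failing both windows.

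| Mean overnight gap | Pass 2 h measure | Pass 4 h measure |
|---|---|---|
| 6 h | 6–76% | 24–99.9% |
| 7 h | 4–51% | 23–99% |
| 8 h | 1–14% | 21–88% |
| 9 h | 0.1–1.3% | 12–52% |

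The 2 h measure approaches the floor when overnight gaps average 8 h or more. The 4 h measure does not.

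**Step 4: daily-count measure, q^7** (q = chance of four doses on a given day): 21% at 0.80, 48% at 0.90, 70% at 0.95. It reaches 5% only at q of about 0.65.

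**Step 5: power of Fisher's exact test, 50 per arm.**

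| Pass rates in the two arms | Power |
|---|---|
| 1% v 5% | 2% |
| 2% v 10% | 19% |
| 5% v 15% | 24% |
| 6% v 25% (p = 0.90 v 0.95) | 68% |

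**Step 6: what a graded measure would separate.** On an even 6-hourly schedule, one dose taken 3 h late makes one gap of 9 h and the next 3 h, so 25 of 27 intervals (93%) are within 6 ± 2 h. The patient in Step 1 has 21 of 27 (78%) within 6 ± 2 h and 27 of 27 within 6 ± 4 h. A patient with, say, 12 of 27 (44%) is clearly different from both, yet all three are identical failures on the planned 2 h measure.

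**The case against.** The strongest reply is that the substudy is mainly descriptive. A low proportion keeping strictly to 6-hourly dosing is then a result in itself. Graded measures of dose-taking are already planned (more than 80% of doses, banded adherence, days to discontinuation), the per-protocol set does not use timing, and a percentage could be computed later from the same openings. All of that stands, and it is why the point is minor. It does not remove the point: the timing measures are also listed for between-arm testing, none of the graded measures uses timing, and the article presents itself as the pre-specified analysis plan.

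A reader might go further in three ways that the article does not support.

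- *Nearly every patient will fail all these measures, whatever the arm.* The article gives no per-interval compliance. Across the range in Step 2 the pass rate runs from 0.2% to 76%, and if timing habits differ between patients it is higher than p^27 at the same average p. The 4 h and daily-count measures need not be low, and 0.90 versus 0.95 per interval would give 6% versus 25%, so a difference between arms is not ruled out.
- *The daily-count measure depends on the hour of attendance.* That holds only if a day means a calendar day. The article does not define it, and such a derivation rule may be left to a fuller plan.
- *Four times daily contradicts 6-hourly.* Four doses in 24 h is nominally one every 6 h, so the two statements are compatible.

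**Conclusion.** The point holds in a limited form. The only listed dose-timing measures are all-or-none over 27 intervals, so they cannot distinguish a single lapse from erratic dosing. The 2 h measure risks a floor effect: about 1–14% passing at a mean overnight gap of 8 h and about 1% or less at 9 h. At pass rates that low, its between-arm comparison has little power with about 50 per arm.

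This rests on reading the window as gaps between doses, an even split of the 100 patients, a two-sided 0.05 level, and assumed overnight gaps and variability that the article does not give. If patients keep overnight gaps near 6–7 h and miss few doses, the 2 h measure is not at the floor. The loss of information from all-or-none scoring remains in every case. Severity is minor: it is limited to the adherence substudy and has no effect on the primary non-inferiority conclusion.

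**What to change.** For each MEMS patient, compute the percentage of inter-dose intervals within 6 ± 2 h and the percentage within 6 ± 4 h. Compare these percentages between arms, for example as a mean or median difference with a 95% CI. State the denominator (recorded intervals, or all 27), because a patient who stops early has few intervals. Keep the planned all-or-none proportions as descriptive lines. The daily-count measure can stay as it is.

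The cost is a sentence or two in the plan and a few lines of extra analysis. No new data are needed, and according to the Current trial status section recruitment had not yet begun.
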